### Primary endpoint

Postoperative complications at 30 days after surgery scored by the CCI, assessed by a blinded, independent expert committee.

### Secondary endpoints

Secondary outcomes are measured before prehabilitation (screening visit) and thereafter (preoperative visit) and at 30 days after surgery (postoperative visit) unless otherwise specified:

#### Cardiovascular and pulmonary

CPET: Peak VO2, VO2 at AT, peak VE, VE/VCO2 slope, oxygen uptake efficiency slope, forced expiratory volume in 1 s (FEV1), FEV1/forced vital capacity, resting HR, HR reserve, resting systolic and diastolic BP.Grip strength.Physical Function Performance 10 Test (CS 10).CPAx ICUD and CPAX HosD in case of ICU admission.MIP.NTproBNP.Serial hs-Troponin-T.Change in preoperative P-POSSUM score.

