### Preoperative assessments

All patients are assessed twice during the preoperative phase, once at inclusion (baseline) and once the day before surgery (preoperative). Measurements conducted during these visits include CPET, grip strength and maximal inspiratory pressure for the assessment of physical fitness. Bioelectrical impedance analysis^13^ measurements and validated nutritional screening and assessment tools (Nutrition Risk Screening 2002 (NRS-2002) and the Subjective Global Assessment [SGA]) will be performed to quantify participants’ body composition and nutritional status. Blood samples are taken to screen for anaemia (haemoglobin, reticulocyte index, renal function, iron status using transferrin saturation), nutritional and diabetic status (albumin, prealbumin, glucose, glycated haemoglobin (HbA1c)), micronutrient deficits (erythrocyte folate, holotranscobalamin, 25-hydroxy-vitamin D) and cardiac function (N-terminal-pro hormone brain-derived natriuretic peptide (NT-proBNP), high-sensitivity (hs) TroponinT). For smokers, exhaled carbon monoxide (CO) is measured (Smokerlyzer Bedfont Scientific, Kent, UK) and smoking habits evaluated by questionnaire including the Fagerström test. All patients are asked to fill in the short form of the State-Trait Anxiety Inventory,^70^ the DASI and (on the day prior to operation) the Quality of Recovery (QoR-)15 questionnaire. An activity tracker (AX3, Axivity, Newcastle, UK) is provided at the screening visit and continuously worn until the preoperative visit, when it is collected from the patient.

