### Group allocation (minimisation)

After completion of the screening visit (CPET), patients who fulfil the inclusion criteria are randomised using computer-generated random numbers, into either intervention or control group. For group allocation, a probabilistic minimisation procedure is used to achieve balanced groups in regard to parameters known to be relevant for outcome after major surgery. We have included the following parameters in the minimisation algorithm (SecuTrial, V.6.1.1.10): type of surgery (visceral, urologic, cardiovascular, orthopaedic, thoracic), smoking, presence of anaemia (haemoglobin below 120 g/L in females, <130 g/L in males), nutritional deficit (NRS ≥3), age group (65–74, 75–84, 85+), ischaemic heart disease or heart failure, known diabetes, sex, obesity (body mass index (BMI) >30 kg/m^2^) and use of extracorporeal circulation.

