#### Intervention group

For patients of the intervention group, we will implement an individually tailored, multimodal prehabilitation programme consisting of physical and respiratory training, correction of nutritional deficits and anaemia and smoking cessation counselling based on the identified deficits.

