### Perioperative management

Perioperative management follows the usual care of the corresponding clinic, usually following standardised, multielement ERAS guidelines. Management decisions such as extension of monitoring and admission to postoperative care (postoperative care unit vs intermediate or intensive care unit (ICU)) are purely based on clinical judgement, taking the results of the preoperative testing into account as it is accessible by the clinicians through the electronic healthcare record system.

In case of raised preoperative NTproBNP >200 pg/mL, hsTroponinT will be measured 6 hours after surgery as well as on the first and second postoperative day.^81^

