### Statistical analysis

Data will be analysed on an intention-to-treat basis (primary outcome). Primary and secondary outcomes for the intervention and control groups will be compared.

Primary outcome: We expect that CCI will be skewed, so we will describe CCI as the median plus first and third quartiles. To test the hypothesis (H0) that the study arms result in similar CCIs (in other words, prehabilitation does not prevent postoperative complications), we will use a generalised linear model that can account for skewed data and zero inflation. The model will be adjusted for the minimisation factors used at randomisation. If no adequate model can be fit, the non-parametric Mann-Whitney U test will be used.

Secondary outcomes: All secondary outcomes will be described as means plus SD or median plus first and third quartiles for continuous data as appropriate. Categorical parameters will be described as frequencies plus percentage per time point. To account for repeat measurements of patients, we will use generalised linear mixed models to test the hypothesis of both study arms being equal in terms of secondary outcomes over time. Models will be adjusted for minimisation factors as well as baseline values (before randomisation) of the respective outcome.

Data distribution will be assessed by visual inspection of Q-Q plots.

As a secondary analysis, we will perform a PP analysis. Since the time between randomisation and surgery might differ between the two randomisation groups, we will additionally adjust generalised linear models of the primary outcome for this factor in a sensitivity analysis. Further, we will analyse the impact of adherence to the interventions to the primary outcome.

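### CPAx is recorded only in patients admitted to ICU, so its planned comparison between arms is made in groups selected after randomisation, with a bias of uncertain direction and size

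*Protocol article*

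**What the plan says.** Under Secondary endpoints (Cardiovascular and pulmonary), the protocol article lists "CPAx ICUD and CPAX HosD in case of ICU admission". The suffixes are not expanded; I read them as ICU discharge and hospital discharge.

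Four other sections bear on this endpoint:

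- **Group allocation (minimisation):** "After completion of the screening visit (CPET), patients who fulfil the inclusion criteria are randomised using computer-generated random numbers". Randomisation therefore precedes prehabilitation, surgery and any ICU stay.
- **Preoperative assessments:** patients are tested at baseline and again the day before surgery. "Measurements conducted during these visits include CPET, grip strength and maximal inspiratory pressure for the assessment of physical fitness".
- **Perioperative management:** decisions on monitoring and on the level of postoperative care, including ICU, "are purely based on clinical judgement, taking the results of the preoperative testing into account".
- **Statistical analysis:** a general sentence says that primary and secondary outcomes of the two groups will be compared. Mixed models are then used "to test the hypothesis of both study arms being equal in terms of secondary outcomes over time", adjusted for the minimisation factors and the pre-randomisation value of each outcome. CPAx is not singled out as descriptive.

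**The concern.** A CPAx value exists only for a patient who was admitted to ICU and, on my reading of the suffixes, lived to discharge. Both are events after randomisation. The programme could influence admission by two routes. It could improve the test results that clinicians consult, since it is a "multimodal prehabilitation programme consisting of physical and respiratory training, correction of nutritional deficits and anaemia and smoking cessation counselling". It could also reduce complications, which is the trial's hypothesis. If either route operates, the ICU patients in the two arms are selected differently, and a difference in CPAx mixes any effect on function with a difference in who was measured. A reader of the results would see a between-arm test listed with the other secondary outcomes and would have no sign that randomisation does not protect it.

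**Working it through.** The plan states no figure for CPAx, so there is nothing to reproduce. I checked the order of events and then illustrated how large the bias could be.

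**Order of events.** Screening CPET, randomisation, prehabilitation or control, testing the day before surgery, surgery, ICU admission or not, CPAx. The selection step follows the intervention. None of the stated safeguards acts on it:

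- The treating anaesthetist is blinded to arm but sees the test results (Blinding procedure), and the intervention may have changed those results.
- The minimisation factors contain no fitness measure.
- A score taken at discharge has no pre-randomisation value to adjust for.
- Intention-to-treat is stated for the primary outcome, and it cannot restore a subset formed afterwards.

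**Assumed inputs (none are in the article).** ICU admission rates per arm; severity standard normal in the control arm; the sickest patients are admitted; correlation 0.6 between severity and CPAx; a higher CPAx is better. Results are in SD of CPAx.

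**Case A: only the admission cut-off moves, and there is no true effect on CPAx.** If the sickest fraction p is admitted, mean severity among those admitted is φ(z)/p, with z the cut-off.

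- p = 50%: 0.798. p = 40%: 0.966. p = 30%: 1.159.
- Admission falls from 50% to 40%: (0.966 − 0.798) × 0.6 = 0.168 × 0.6 = 0.10 SD worse with prehabilitation. Correlations of 0.4 and 0.8 give 0.07 and 0.13 SD.
- Admission falls from 40% to 30%: (1.159 − 0.966) × 0.6 = 0.193 × 0.6 = 0.12 SD worse.

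**Case B: severity itself falls and the cut-off stays fixed.** A fall of 0.253 SD also takes admission from 50% to 40%.

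- Mean severity of admitted intervention patients: 0.966 − 0.253 = 0.713, against 0.798 in control.
- Apparent difference: (0.798 − 0.713) × 0.6 ≈ 0.05 SD better with prehabilitation.
- True difference in all patients: 0.253 × 0.6 ≈ 0.15 SD better.

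The sign is right, and about one third of the benefit is visible.

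**Case C: softer selection, by simulation (1,000,000 patients per scenario).** Prehabilitation raises fitness by 0.4 SD. Admission depends on fitness, unmeasured severity and noise. Control admission is 20%, 40% or 60%; at 40% it falls to about 30% with prehabilitation.

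| True difference, all patients | ICU-only difference |
|---|---|
| none | −0.06 to −0.08 SD |
| about +0.06 SD | −0.03 to −0.04 SD |
| about +0.10 SD | −0.02 to +0.01 SD |
| about +0.22 SD | +0.10 to +0.14 SD |

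**Case D: as C, with a further 30% admitted whatever their results.** With no true effect the ICU-only difference is −0.02 to +0.02 SD. With a true benefit it stays positive, between 0.03 SD below and 0.04 SD above the true value.

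**Set against precision.** The Sample size section gives 388 analysed, or 194 per arm. At 50% and 40% admission, 194 × 0.5 = 97 and 194 × 0.4 ≈ 78 patients have CPAx. The standard error of the difference is at most about √(1/97 + 1/78) ≈ 0.15 SD. The 0.10 SD of Case A is then about 0.7 standard errors, which would raise a nominal 5% two-sided rejection rate to roughly 10–11%.

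**The case against.** The strongest reply has four parts.

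1. **Direction.** A reader might infer that the comparison will point against an effective programme, because those still admitted are a sicker remainder. The documents do not support this as a general statement. It needs the cut-off to move while severity stays put. If the programme works by lowering severity, Case B gives an attenuated benefit with the right sign. In the simulation a clear reversal appeared only at a very small true benefit (+0.06 SD). This part stands.
2. **Size.** Case A is near the worst case: the sickest are admitted exactly, with no noise and no routine admission. Table 1 shows 14 of the first 18 patients at ASA IV or above and 5 of 18 with extracorporeal circulation. Substantial routine admission is therefore plausible, although the article does not say so. This part stands too.
3. **Which results and which model.** The section headed Preoperative assessments covers both visits, so the results that clinicians consult can include baseline values that prehabilitation cannot have altered. The mixed model for outcomes over time does not fit a discharge score cleanly. Both remarks are fair. But the results from the day before surgery are included as well, and the general sentence that secondary outcomes will be compared remains.
4. **Level of detail.** Whether a single secondary endpoint is tested or only described is often settled in a statistical analysis plan, and none is shown here. If such a plan already makes CPAx descriptive, the point is met. The article itself, however, fixes both the restricted population and the comparison.

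**Conclusion.** The structural point holds. As written, CPAx would be compared between arms in a subset formed after randomisation, by a decision that the intervention can influence, and nothing in the stated analysis corrects for this.

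Direction and size are uncertain because the article gives neither ICU admission rates nor the spread of CPAx. Under the stated assumptions the bias runs from about 0.1 SD against the programme (no true effect, only the cut-off moves), through attenuation of a real benefit, to near zero if many admissions are routine. It would also go too far to call the test meaningless: where admission is largely routine in both arms, the comparison would be close to the randomised one.

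One secondary endpoint is affected. The primary endpoint, CCI at 30 days, does not depend on ICU admission and is untouched. Severity: minor.

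**What to change.** Take CPAx out of the outcomes tested between arms. Report, per arm and in all operated patients, the number admitted to ICU and the number who died before discharge. Give CPAx descriptively beside those counts, with a sentence saying that it is not a randomised comparison.

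I would not substitute a test restricted to patients with planned extracorporeal circulation. It assumes that admission is routine in that group, which the article does not state. It would keep only about a quarter of patients (5 of the first 18), and selection by death before discharge would remain.

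The cost is one secondary hypothesis test. No new data are needed, and nothing changes in how admission is decided.

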#### Nutrition and bioimpedance

NRS 2002.PG-SGABioelectrical impedance analysis: weight, muscle mass, fat mass, percent body fat, extracellular water/intracellular water, phase angle, fat free body mass.Days nil per mouth (only at postoperative visit).

#### Anaemia

Presence of anaemia.Transfusion in the first 30 days after surgery.

#### Smoking

Average number of cigarettes per day, Fagerström-Score.Exhaled CO.

#### Patient-reported outcomes

QoR-15.State-Trait Anxiety Inventory.^70^DASI.

#### Other outcomes of interest

Length of hospital stay.Days at home at 30 days.Predicted costs for visceral interventions.CCI at 30 days postoperative assessed by the treating physician (unblinded).CCI at 90 days postoperative assessed by the treating physician (unblinded).

#### Safety outcomes

Days to surgery.(Serious) adverse events.

### Sample size

Based on internal data (Bern University Hospital), median CCI is expected to be 30 (IQR 21–37). Assuming an average clinically relevant improvement of 15% in the intervention group compared with the control group, the sample size calculation for a non-parametric Wilcoxon-Mann-Whitney test resulted in a total patient sample of 388 (assuming a significance level alpha of 0.05 and power of 0.80). We expect a dropout rate of 20%. We, therefore, need 466 patients: 233 in each arm. We aim to complete the inclusion within 3 years.

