**Methods and analysis:**

This is a multicentre, multidisciplinary, prospective, 2-arm parallel-group, randomised, controlled trial with blinded outcome assessment. Primary outcome is the Comprehensive Complications Index at 30 days. Within 3 years, we aim to include 2×233 patients with a proven fitness deficit undergoing major surgery to be randomised using a computer-generated random numbers and a minimisation technique. The study intervention consists of a structured, multimodal, multidisciplinary prehabilitation programme over 2–4 weeks addressing deficits in physical fitness and nutrition, diabetes control, correction of anaemia and smoking cessation versus standard of care.

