## Methods

### Study design

This is a national multicentre, multidisciplinary, prospective, two-arm parallel-group, randomised, controlled superiority trial with blinded outcome assessment. We aim to include 466 patients within 3 years. The present protocol complies with the Standard Protocol Items: Recommendations for Interventional Trials (SPIRIT) 2013 guidelines, defining standard protocol items for clinical trials.

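### Minor correction: the 20% dropout allowance was multiplied on (388 × 1.2 = 466) instead of divided out (388 / 0.8 = 485), so 466 leaves about 373 evaluable patients, not 388

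*Protocol article*

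**What the plan says.** The protocol article sets out the calculation in one short run under Sample size. The sizing step for a Wilcoxon-Mann-Whitney test "resulted in a total patient sample of 388 (assuming a significance level alpha of 0.05 and power of 0.80"). The dropout allowance follows directly: "We expect a dropout rate of 20%. We, therefore, need 466 patients: 233 in each arm".

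The result appears in two other places. The abstract (Methods and analysis) says "we aim to include 2×233 patients with a proven fitness deficit", and the Study design section says "We aim to include 466 patients within 3 years". Neither gives a dropout rate or a power. The article states no other dropout rate and no other rule for inflating the sample size.

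**The concern.** The second sentence presents 466 as what follows from 388 and a 20% loss. Removing 20% from 466 does not return 388, so the enrolment target, the expected dropout and the stated power cannot all hold together.

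What is at stake is the accuracy of the power claim for the primary endpoint. Readers will rely on that claim when they interpret the result, above all a null one. The error runs in the unfavourable direction: at the dropout that the trial itself expects, it falls slightly below the power it claims, and a planned power of 80% leaves little slack.

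**Working it through.** **Inputs, all from the Sample size section**
- Evaluable patients required: 388 in total, or 194 per arm at 1:1.
- Expected dropout: 20%.
- Stated target: 466, or 233 per arm.
- Alpha 0.05 and power 0.80. The section does not say whether the test is one- or two-sided; two-sided is assumed here.

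**Step 1. Reproduce the plan's figure.** Multiplying up: n × (1 + d) = 388 × 1.20 = 465.6, rounded up to 466. This matches exactly.

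**Step 2. The inflation that keeps 388 after a 20% loss.** n / (1 − d) = 388 / 0.80 = 485. With equal arms, 194 / 0.80 = 242.5, rounded up to 243 per arm, or 486 in total. This is 486 − 466 = 20 more than stated (20 / 466 = 4.3%).

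**Step 3. What 466 leaves at 20% dropout.** 466 × 0.80 = 372.8, about 373 in total and about 186 per arm. The shortfall is 388 − 372.8 = 15.2 patients, or 15.2 / 388 = 3.9%.

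**Step 4. The dropout that 466 does cover.** 1 − 388 / 466 = 0.167, or 16.7%.

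**Step 5. Power at 373, taking 388 to give exactly 80%.** By the normal approximation, the expected test statistic scales with the square root of the sample size:

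power(N) = Φ[(1.960 + 0.842) × √(N / 388) − 1.960]

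- N = 388: Φ(0.842) = 0.800, as planned.
- N = 373: √(373 / 388) = 0.9805; 2.8016 × 0.9805 − 1.960 = 0.787; Φ(0.787) = 0.784.

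The loss is about 1.6 percentage points. Sidedness matters little. With a one-sided 0.05 test, (1.645 + 0.842) × 0.9805 − 1.645 = 0.793 and Φ(0.793) = 0.786.

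**The case against.** The strongest case on the other side accepts the sum and disputes its weight.

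- **The effect is small.** About 15 evaluable patients and 1.6 points of power are well within the uncertainty of the planning inputs, which are an assumed 15% improvement and one hospital's internal data. If dropout turns out at 16.7% or less, 466 delivers 388. Bias, type I error and the estimand are untouched. This stands, and it is why the point is a minor correction. A reader might infer that the trial is seriously underpowered or has to recruit more patients; the figures do not support that.

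- **The 78% is conditional.** It assumes that 388 gives 80% for the Wilcoxon-Mann-Whitney sizing test. The Statistical analysis section makes the primary analysis a generalised linear model suited to skewed, zero-inflated data and adjusted for the minimisation factors, with Mann-Whitney as the fallback. The power of that model may be higher or lower and cannot be worked out from the article. This stands: 78% is not the established power of the planned primary analysis.

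- **388 itself cannot be rebuilt from the printed summary.** A shift of 0.15 × 30 = 4.5 points with an SD of (37 − 21) / 1.349 = 11.9, taken as normal, needs only about 220 to 256 patients, depending on the approximation. A reader might infer that 388 is wrong, or that 373 is more than enough. Neither follows, because the calculation may have used the skewed internal data, which are not shown. The inflation step fails whatever produced 388.

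- **Dropout may not mean loss of the primary outcome.** The analysis is by intention to treat, patients who stop the programme can still have a 30-day CCI, and death scores 100 on that index and is not lost. Fewer than 20% may therefore be missing from the primary analysis. This weakens any forecast that only 373 will be analysed. It does not repair the sentence, because the protocol itself sets the allowance against a 20% loss.

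**Conclusion.** The sentence is wrong as written, and the correction is minor. Only 388 × 1.2 reproduces 466. An allowance that meets the stated 20% would be 485, or 486 with equal arms.

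At 20% dropout, the target leaves about 373 evaluable patients where 388 were required, a shortfall of about 15 (3.9%). Power for the sizing test is then about 78% where 80% was claimed. The arithmetic on patient numbers rests on the printed figures alone. The power figure rests on three assumptions: that 388 gives 80%, that the test is two-sided at 0.05, and that the 20% are lost to the primary analysis.

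A reader might also infer that the abstract and the Study design section are wrong. They state only 2×233 and 466, with no dropout or power attached, and both remain correct as long as 466 is kept.

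**What to change.** Keep 466 and replace the dropout sentence in the Sample size section with wording such as: *With the expected 20% dropout, 466 randomised patients (233 per arm) leave about 373 evaluable, giving about 78% power; 80% power is kept if dropout is at most 16.7%.* The sponsor can substitute the power that its own sizing calculation returns at about 186 per arm.

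The cost is one sentence and a slightly less favourable power figure. No extra patients are needed, and no other section changes.

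If the sponsor prefers to keep both 20% dropout and 80% power, the target becomes 486 (243 per arm), which is 20 more patients. Only then must the abstract and the Study design section be changed to match.
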